## Abstract

**Background:**

Nosocomial infections are the most common complication during inpatient hospital care. An increasing proportion of these infections are caused by multidrug-resistant organisms (MDROs). This report describes an intervention study which was designed to address the practical problems encountered in trying to avoid and treat infections caused by MDROs. The aim of the HARMONIC (Harmonized Approach to avert Multidrug-resistant Organisms and Nosocomial Infections) study is to provide comprehensive support to hospitals in a defined study area in north-east Germany, to meet statutory requirements. To this end, a multimodal system of hygiene management was implemented in the participating hospitals.

**Methods/design:**

HARMONIC is a controlled intervention study conducted in eight acute care hospitals in the ‘Health Region Baltic Sea Coast’ in Germany. The intervention measures include the provision of written recommendations on methicillin-resistant Staphylococcus aureus (MRSA), vancomycin-resistant Enterococci (VRE) and multi-resistant Gram-negative bacteria (MRGN), supplemented by regional recommendations for antibiotic prescriptions. In addition, there is theoretical and practical training of health care workers (HCWs) in the prevention and handling of MDROs, as well as targeted and critically gauged applications of antibiotics.

The main outcomes of the implementation and analysis of the HARMONIC study are: (i) screening rates for MRSA, VRE and MRGN in high-risk patients, (ii) the frequency of MRSA decolonization, (iii) the level of knowledge of HCWs concerning MDROs, and (iv) specific types and amounts of antibiotics used.

The data are predominantly obtained by paper-based questionnaires and documentation sheets. A computer-assisted workflow-based documentation system was developed in order to provide support to the participating facilities. The investigation includes three nested studies on risk profiles of MDROs, health-related quality of life, and cost analysis. A six-month follow-up study investigates the quality of life after discharge, the long-term costs of the treatment of infections caused by MDROs, and the sustainability of MRSA eradication.

**Discussion:**

The aim of this study is to implement and evaluate an area-wide harmonized hygiene program to control the nosocomial spreading of MDROs. Comparability between the intervention and control group is ensured by matching the hospitals according to size (number of discharges per year / number of beds) and level of care (standard or maximum). The results of the study may provide important indications for the implementation of regional MDRO management programs.

## Background

Nosocomial infections are the most common complication that can occur during inpatient hospital care [1], and antimicrobial resistance is a serious threat to public health [2]. The Second European Point Prevalence Survey 2011–2012, involving 30 countries, showed that 6.0 % of the 231,459 surveyed patients had a healthcare-associated infection. The prevalence varied widely depending on country and type of ward, however [3]. In a sample of 9,626 patients from 46 hospitals in Germany, 5.1 % suffered from a nosocomial infection. 66 % of those infections (3.4 % of the whole sample) had arisen during the current hospital stay [4]. A significant proportion of these infections are caused by multidrug-resistant organisms (MDROs), with methicillin-resistant *Staphylococcus aureus* (MRSA) as the main cause [5, 6].

In Germany, the prevalence of MRSA has been nearly stable in recent years, with an 18 to 20 % resistance rate in clinical *Staphylococcus aureus* isolates [7]. It has, on the other hand, slightly decreased in high risk settings such as intensive care and surgical wards, where the proportion of MRSA among nosocomial *Staphylococcus aureus* infections decreased from 33 % to 27 % in the period from 2007 to 2012 [8]. In contrast, there has been a rise in the number of multiresistant Gram-negative bacteria (MRGN), such as third-generation cephalosporin (3GC)-resistant *Escherichia coli* and 3GC-resistant *Klebsiella pneumoniae* [9–12]. The prevalence of vancomycin resistance is also increasing in Germany, but this is mainly restricted to strains of *E. faecium*. The rate of vancomycin resistance in clinical *E. faecium* isolates varies between 8 and 15 %, with local and regional variability ranging from 0 % to over 30 % [13].

International studies have shown that between 10 and 70 % of nosocomial infections could have been prevented. Important factors involved in this variation were setting, study design, baseline infection rates and type of infection [14].

When planning infection control measures, it has to be taken into consideration that patients move freely between acute care and rehabilitation facilities, as well as within the ambulant sector [15]. Therefore, hospitals should not be viewed as isolated units, but rather as connected elements of a larger modular network, requiring a regional approach [16]. In the Baltic Sea Coast region, the joint research project HICARE (Health, Innovative Care And Regional Economy) was initiated in 2011 to improve control of MDROs in north-east Germany. HICARE is supported by public funds and supplemented by industrial contributions. A basic element of the HICARE project is the implementation of a multimodal hygiene program in the acute care hospitals of the region, which was developed within the framework of the HICARE project and included all German statutory specifications for infection protection. The governmental recommendations for the prevention and control of multiresistant organisms are mandatory for medical facilities, as specified by the July 2011 revision of the German *Infection Protection Act* (Infektionsschutzgesetz) [17]. To date, nationwide mandatory recommendations have been issued for MRSA [18–20] and, more recently, for MRGN [9, 21]. In addition to these two groups of causative organisms, the HICARE program includes recommendations for dealing with VRE.

To include the patient’s point of view and experience, the current study contains a patient evaluation sheet on hospital hygiene practice, and examines as well the health-related quality of life of patients with MDROs. Only few studies have been published on these aspects. Analyses of the costs and benefits of measures to reduce multidrug-resistant organisms are also scarce in Germany [22, 23].

One problem that arises with pre- and post-studies to determine the effects of intervention measures is the fact that changes in statutory requirements over time often affect the results. Therefore, the present study is designed as a prospective, controlled intervention study. Since the goal is to implement the HICARE hygiene program in all participating hospitals, those in the control group will obtain the intervention measures immediately after completion of the study phase I (delayed-intervention group; see also Fig. 2).

The primary objectives of the intervention are:Early detection of MDRO carriers to prevent complications and transmissions to other patients and hospital personnel through consistent hygiene measuresImprovement in decolonization of MRSA patientsImprovement in regional resistance profiles by a targeted and critically assessed use of antibiotics

As this study focuses on the area-wide implementation of statutory regulations, it is strictly speaking not a clinical study, and it was therefore not registered as a clinical trial. The Ethics Committee approval numbers are: BB 64/12 (Medical Committee of the University Medicine Greifswald) and A 2013–0037 (Medical Ethics Committee of the University Medicine Rostock).

## Methods and design

### Design overview and setting

A total of 12 hospitals providing acute care participate in the HICARE project. Due to lack of personnel and time resources, four of these hospitals could not participate in the HARMONIC study. Therefore, the study was conducted in eight hospitals in the Health Region Baltic Sea Coast in Germany (Fig. 1). The study was designed as an 18-month prospective intervention study, which aims at implementing a multimodal hygiene management program. The recruitment of study hospitals started right after ethics approval (29th of May 2012). Hospitals were randomized concerning the immediate implementation of the intervention program *versus* the campaign starting with a six-month delay, in four strata of two hospitals each. The strata were defined by level of care (maximum care *versus* standard care) and hospital size (>25,000; 10,000 to 25,000; 5,000 to 10,000; and < 5,000 annual discharges). Table 1 shows the characteristics used to match the participating hospitals in according pairs. The hospitals in the delayed-intervention group received the intervention measures after completion of the first phase of the study (Fig. 2). Data collection started in February 2013 and was finished for the main study in November 2014. Analysis will be finished in June 2015 and December 2015 for two of the nested studies.

**Fig. 1 Fig1:**
[figure not shown]
Health Region Baltic Sea Coast — hospitals participating in the study

**Table 1 Tab1:** Characteristics used to match the study hospitals

	Number of discharges/year^a^	Number of beds^a^	Level of care^b^	Matching pair
	(Precision: 10^3^)	(Precision: 10^2^)		
Hospital 1	40,000	1,000	maximum	A
Hospital 2	35,000	900	maximum	A
Hospital 3	23,000	500	standard	B
Hospital 4	10,000	200	standard	B
Hospital 5	7,000	200	standard	C
Hospital 6	7,000	100	standard	C
Hospital 7	4,000	100	standard	D
Hospital 8	4,000	100	standard	D

^**a**^Data refer to the year 2010

^**b**^Levels of care (maximum care or standard care)

-maximum care hospitals: tertiary care; major hospitals with specific sub-specialty care

-standard care hospitals: secondary care; the range of services is restricted to prevalent conditions and a typical range of risks

**Fig. 2 Fig2:**
[figure not shown]
Cluster-specific study phases

Data were collected at the beginning and the end of each study phase. These data include structural data and the level of knowledge of hospital personnel with regard to MDROs. Furthermore, patients in selected wards were monitored for a period of six months in each study phase (see also Fig. 2). To maximize comparability of the participating hospitals, data were obtained for comparable subsets of three wards, each including a conservative intensive care ward, an internal medicine ward and a surgical ward. According to the specific structure and procedures of the hospital, an emergency ward was also included where applicable.

Various groups of MDROs were investigated in this study: MRSA, VRE and MRGN. Multiresistant Gram-negative organisms were defined according to the guidelines of KRINKO (German commission for hospital hygiene and infection protection) for MRGN [21]. This classifies MRGN into three groups, based on the susceptibility to four of the most clinically important groups of antibiotics (*acylureidopenicillins*, *quinolones*, 3rd gen. *cephalosporines*, *carbapenems*): 3MRGN is resistant to three of the four groups, 4MRGN is resistant to four of the four groups, and strains resistant to less than three groups are classified as non-multiresistant. The underlying mechanisms (e.g. ESBL, CPE) are not considered in this classification. Since the ability to accumulate extended-spectrum beta-lactamase (ESBL) is still partly used to categorize organisms, this was also included in the data collection.

The facilities participating in this study are acute care hospitals in the Health Region Baltic Sea Coast and adjacent hospitals, including two hospitals with maximum care status (tertiary care; major hospitals with specific sub-specialty care), and six public and private acute care hospitals with basic and standard care (secondary care; the range of services is restricted to prevalent conditions and a typical range of risks).

### Recruitment of patients and informed consent

Written informed consent was obtained for participation in this study. The patients could accept or refuse certain aspects of participating in the study: the forwarding of personal data to an independent trust agent, the pseudonymized storage of treatment data in a research database, the possibility of being recontacted at a later date for follow-up purposes, and the authorization to contact health care-related people or institutions, such as their family doctors or health insurance. Basic, anonymous information on refusal was tracked (gender and age) and considered in the analysis.

### Hypotheses

The intervention is expected to lead to:An increased screening rate of persons at risk for MDROsAn increase in MRSA decolonization where indicatedAn increase in knowledge of the healthcare personnel about the prevention and handling of MDROs, e.g. treatment of infectionsA lower rate of antibiotic prescriptionsA higher use of hand and surface disinfectants

### Intervention / hygiene measures

The HICARE intervention is based on (A) system change (hygiene regime) and (B) behavior change methods:

 (A) Existing hygiene regimes of the participating hospitals were adapted to the HICARE hygiene program by a joint coordination process (harmonized approach). A goal plan was set up to support necessary improvements, based on a comparison of the status quo and the targets of the intervention, documented via a standardized table sheet. While planning the implementation of the intervention, findings to change management in the field of hygiene measures were considered [24]. For example, it was important to continuously interact with the responsible hygiene specialists at each study site (doctors and nursing staff). These persons also acted as coordinators on site.

(B) To accomplish behavioral change, behavior-centered theoretical frameworks were taken into consideration [25–27]. Key aspects from multiple domains were addressed during conception of the intervention, such as: knowledge, skills, self-efficacy, beliefs about consequences, motivation and goals, memory, attention and decision processes, and the environmental context and resources (e.g. physical resources, management aspects). Several behavior change methods were taken into account [26, 28] and applied to the different modules of the intervention.

Evidence-based, pathogen-specific recommendations for the prevention and handling of MRSA, VRE and MRGN were drafted within the framework of the HICARE program, including governmental recommendations. The HICARE recommendations, which also include regional recommendations for the initial prescription of antibiotics for adults, represent the basis for the intervention.

The constituent parts of the intervention and the measures to promote the implementation are described in Table 2.

**Table 2 Tab2:** Constituent parts of the intervention and measures to promote the implementation

Constituent parts of the intervention	Measures to promote the implementation
1. Theoretical and practical training courses for HCWs by the study team in: risk-based MDRO screening, isolation in suspected and confirmed cases of MDRO, treatment of MDRO cases including evidence-based decolonization protocol for MRSA, general measures to prevent MDROs (standard hygienic measures such as disinfection of hands and bed site surfaces, protective clothing)	For each hospital, together with the coordinator on-site, several alternative appointments were set up for each training course. Thus, it was possible that nearly all HCWs of the participating wards could join the courses. The courses were registered by the medical associations as advanced training, which adds to the attractiveness of the course.
2. Instructions on treatment of MDRO including an evidence-based decolonization protocol for MRSA ( The first line therapy for MRSA decolonization in the HARMONIC intervention was Mupirocin nasal ointment. In case of Mupirocin-resistance, polihexanide nasal ointment was used. For antisepsis of buccal cavity octenidine is used, alternatively polihexanide.)	The computer-assisted system ensures the implementation of the intervention by a step by step guidance. Pocket cards for the decolonization protocol for MRSA were provided.
3. Instruction courses by the study team for physicians on the recommendations for use of antibiotics	Several alternative appointments were offered to achieve a high participation rate. The courses were registered by the medical associations as advanced training, which adds to the attractiveness of the course.
4. Provision of detailed information material on the intervention	A folder with the course material was available on each ward. Information was additionally provided *via* a study website (separate log in for intervention hospitals).
5. Posters to intervention measures and application of study instruments	They function as a reminder.
6. Pocket cards for screening regime and decolonization protocol, see also point 2.	They function as a reminder.
7. Periodic on-site visits by the study team to provide advisory support on the implementation of the intervention measures and documentation of the improvement	The documentation was done *via* table structure and text fields. Feedback on performance was given (sources: on-site visits and monitoring process)
8. Provision of a “hotline” for questions to the intervention measures, manned by experts in hospital hygiene, who belonged to the study team	Requests of HCWs of the participating wards to single intervention measures could be answered timely. Furthermore, questions were documented anonymously and are used in the evaluation process of the study.
9. Provision of information material for patients (booklets on different MDROs)	The material supports patient information and education.

### Screening and diagnostic procedure

The following sites were screened for MRSA, according to the HARMONIC intervention: pooled nasal swab (both nostrils), throat and wounds or catheter positions if infected by bacterial culture. The laboratory diagnosis of MRSA differs in the participating hospitals, depending on availability of methods:PCR, if PCR is positive: confirmation by culture,only by culture *or*mainly by culture, unless a fast result by PCR is necessary.

Sites of screening for VRE include stool samples, and in exceptional cases rectal swabs. Detection of VRE is done by culture.

Sites of screening for MRGN are:Enterobacteria: stool sample and rectal swab; anatomic sites with former positive MRGN results; materials from potentially infected body fluids such as urine, wound secretions, tracheal secrete, blood culture and further stool samples or rectal swabs,Multiresistant non-fermenting organisms: throat swab, large-scale skin swab (*A. baumannii*).

Diagnostic results are obtained by culture.

### Collaboration with industry

The research institutions that organized this joint project cooperate with the healthcare management companies that take part in the HICARE project, as requested by the federal funding organization. The following materials used during the intervention phase were provided by the companies: automatic hand disinfectant dispensers, sterile water filters for intensive care wards, confectioned MRSA treatment kits for standardized decolonization, and care gowns that are impermeable for pathogens for barrier nursing.

### Outcome measures

Primary outcome:Screening rates for MRSA, VRE and MRGN in risk patients

Secondary outcomes:Frequency of MRSA decolonization upon indicationLevel of knowledge about MDROs by the nursing staff and physiciansTypes and amounts of antibiotics useUse of hand and surface disinfectants

### Nested studies

#### Analysis of risk profiles for multidrug-resistant organisms in patients screened for MDROs

The risk profiles of patients who tested positive for MDROs at admission was compared to patients who tested negative. Analyses will be performed for MDROs in general, as well as for individual groups of pathogens, as examined in the HARMONIC study.

#### Analysis of health-related quality of life of MDRO carriers

To define the impact of MDRO infection or carriership on quality of life, a matched analysis was performed (ratio 1:1). The health-related quality of life for patients who tested positive for MDROs will be compared to patients who tested negative and who were admitted in the participating wards of the same hospital. Matching criteria will include sex, age (+/− 5 years) and severity of illness. The patient-reported SF-36 Health Survey as modified for use in a hospital setting [29] is to be filled out shortly before discharge from the participating ward.

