#### Analysis of MDRO-related hospital costs

A further study will assess the costs of MDRO management in hospitalized patients. The analysis is based on the data from the documentation sheet on the progression of MDRO status, and from the documentation sheet for nursing efforts. Additionally, lengths of hospital stay and other parameters relating to the German Diagnosis Related Group payment system will be evaluated with a focus on remuneration effects. MDRO-positive patients will be compared with MDRO-negative patients (separately for each pathogen) via matching analysis (ratio 1:3). Matching variables are the main discharge diagnosis (ICD-10) and the type of discharging ward.

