### Methods of data collection and variables

Baseline data collection conducted with participating hospitals included a questionnaire to assess structural parameters (e.g. number of beds/cases/single rooms, staffing ratio, staff level of qualification, prevalence of advanced training in hygiene), and process parameters (procedures of registering, documentation and reporting of MDROs). At the end of each study phase (Fig. 2), potential changes in structural or process parameters were documented, together with use of antibiotics and disinfectants for the given period.Data on the use of antibiotics and disinfectants over the three years prior to this study, as well as test utilization and resulting positive MDRO rates, were documented by the study team.The level of knowledge of the nursing staff and physicians on MDROs was assessed by a multiple choice test at the beginning of the instructional courses.Structured questionnaires and documentation forms were used during the intervention period, and, for the delayed-intervention group only, during the observation period, identical for all hospitals (Table 3).

**Table 3 Tab3:** Documents used for data acquisition during the intervention and observation phase

Documents used in the intervention and observation phase	Description of data collected	Document to be filled out by
Patient admission sheet	Risk factors for MDRO colonization or infection	Health care workers during anamnesis, or, alternatively, by the patient (with help of staff)
Documentation sheet on the progression of MDRO status including transition section^**a**^ for the physician responsible for subsequent treatment	Admission and discharge data, sample taking and diagnosis, where applicable isolation measures, control swab test, time of infection, information for physician responsible for subsequent treatment	Health care workers
Documentation sheet for nursing efforts for MDRO^b^ infections/colonizations	Nursing workload in minutes	Nursing staff
Patient evaluation sheet	Subjective evaluation of hygiene measures in the hospital	Patient
Quality of life questionnaire (modified version of the SF-36)	Health-related quality of life in the last seven days	Patient

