^**a**^This form differs slightly for the delayed intervention group and the immediate intervention group. In order to exert as little influence as possible on the documentation of previous hygiene management programs, the form for the delayed intervention group does not include the transition section for the physician responsible for subsequent treatment

^b^also relevant for reimbursement by the statutory health insurance

Note: Documents can be downloaded from: http://www2.medizin.uni-greifswald.de/icm/index.php?id=hicare

The usage of the questionnaires for the collection of patient data is shown in the flow chart in Fig. 3. Participation was only requested if the patient was expected to remain in the ward for at least 48 hours. The patient admission sheet and both MDRO documentation sheets were designed to replace the previous documentation used by the hospitals. This measure also avoids time and effort of double documentation. The treatment sheets are designed such that the original has space for a label with the patient’s identification and is included in the patient’s file as treatment documentation after the patient is discharged. For the sake of data privacy protection, the carbon copy that is used for our concomitant research will not have a label with patient identifying data. Both the original and the carbon copy are provided with a document barcode, allowing a mapping of multiple documents to a single pseudonym and preserving anonymity for non-consenters.

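### The in-hospital quality-of-life study does not match on ward type, so a valid pair may compare patients leaving different kinds of ward

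*Protocol article*

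**What the plan says.** The section on health-related quality of life of MDRO carriers sets a 1:1 matched comparison. Controls are "patients who tested negative and who were admitted in the participating wards of the same hospital". The criteria are given as: "Matching criteria will include sex, age (+/− 5 years) and severity of illness". The modified SF-36 "is to be filled out shortly before discharge from the participating ward", and Table 3 gives its content as "Health-related quality of life in the last seven days".

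The design section says each hospital contributes three wards, "each including a conservative intensive care ward, an internal medicine ward and a surgical ward", with an emergency ward added where applicable. On entry, the data-collection section says: "Participation was only requested if the patient was expected to remain in the ward for at least 48 hours".

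For the cost study, the article says: "Matching variables are the main discharge diagnosis (ICD-10) and the type of discharging ward".

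The Data analysis section plans t-tests for the matched groups. It also plans multivariate methods, logistic regression in particular, for selected issues, without naming the covariates.

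**The concern.** Self-reported health on leaving a ward depends on the kind of ward. Leaving intensive care and leaving an internal medicine or surgical ward are different moments in an illness. The matching rule fixes hospital, sex, age band and severity, but leaves ward type free.

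If MDRO-positive patients are spread over ward types differently from the negatives chosen for them, the difference in setting becomes part of what is reported as the impact of carriage or infection on quality of life. Such an imbalance is plausible: the Background section treats intensive care and surgical wards as high-risk settings for MRSA.

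A second, smaller issue is what the seven recalled days contain. A patient who leaves after a short stay reports partly on days before admission; one who leaves after a week or more reports on hospital days only.

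**Working it through.** **The plan's own figure.** The article states no sample size or power for the quality-of-life study, so there is nothing to reproduce on this point. Its only power statement concerns the screening rate: 60% against 90%, 1,000 patients per group, alpha 0.05. Treating patients as independent, this gives 1.00 as stated, but it has no bearing here.

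**Step 1: what a valid pair may look like.**

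| Feature | Quality-of-life study | Cost study |
|---|---|---|
| Ratio | 1:1 | 1:3 |
| Same hospital | yes | not stated |
| Sex, age, severity | listed | not listed |
| Main discharge diagnosis | not listed | listed |
| Ward type | not listed | listed |

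Nothing listed in the left-hand column prevents a pair whose members left different kinds of ward.

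**Step 2: how often pairs could be mixed.** If pairs formed without regard to ward, the chance of a mixed pair is 1 − Σp_k², where p_k is the share of patients in ward type k. The article gives no ward mix, so these shares are assumptions:

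- three equal wards: 1 − 3 × (1/3)² = 0.67
- 10/45/45%: 1 − (0.01 + 0.2025 + 0.2025) = 0.585
- four equal wards: 1 − 4 × (1/4)² = 0.75
- 5/30/65%: 1 − (0.0025 + 0.09 + 0.4225) = 0.485

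The range is about 49% to 75%. Matching on severity would lower it by an unknown amount.

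**Step 3: when mixing becomes bias.** Mixed pairs alone only add noise. Bias arises when the ward mix differs between the two groups. It equals Σ(p_k,positive − p_k,negative) × m_k, where m_k is the mean score on leaving ward type k. The article gives neither the two mixes nor the m_k, so neither size nor sign can be computed.

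**Step 4: the seven-day window.** For a patient admitted from home, the share of the window in hospital is min(stay, 7)/7:

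- 2 days: 2/7 = 29%
- 3 days: 3/7 = 43%
- 5 days: 5/7 = 71%
- 7 days or more: 100%

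Two members of a pair may thus differ by up to 5 of 7 days. The lower end is approximate, because 48 hours is an expected and not an observed stay, and because a patient transferred from another ward brings earlier hospital days.

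**Step 5: supply of controls.** From the sample-size section, 5,000 admissions × 40% at risk = 2,000. Screening 60% to 90% of these gives 1,200 to 1,800. Over 24 wards that averages 1,200/24 = 50 to 1,800/24 = 75 screened patients per ward. The 50 to 150 expected MRSA positives average 50/24 = 2.1 to 150/24 = 6.3 per ward. These are averages before consent, form completion and the other matching criteria, and before VRE and MRGN positives are counted.

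**The case against.** The best defence has five parts.

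- **The criteria list is open.** The wording says what the criteria will include, so ward type is not excluded, and the Data analysis section allows covariate adjustment. This stands as far as it goes: pairs may differ, not must. In a condensed article, unnamed covariates are no fault. But the article chose to name criteria, and ward type is named for one matched study and not for the other.
- **Severity is already matched.** It may well separate intensive care from general wards. That is fair, and it lowers the mixed-pair figures. It need not separate internal medicine from surgery.
- **The cost study differs in purpose.** Its focus on remuneration justifies another matching set. Agreed: the contrast shows that ward type is a workable matching variable in this study, not that the plan contradicts itself.
- **Length of stay may result from carriage.** Isolation, control swabs and treatment can prolong it, so matching on stay could remove part of the effect under study. This stands, and it rules out stay as a matching variable.
- **Controls may run short.** In the smaller hospitals, same-ward-type matching on top of sex, age and severity may leave some positives unmatched. This stands as a cost, and is why adjustment is offered as a fallback.

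A reader might also infer a bias of a known number of points. If a hospital day scored 20 points below a day at home, a 9-day positive paired with a 4-day negative would show 20 × 3/7 = 8.6 points, and with a 2-day negative 20 × 5/7 = 14.3. The documents do not support this. They give no such gap, and the days before an acute admission may be worse than those before discharge, which would reverse the sign. Part of the difference in stay may also be a real consequence of carriage.

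**Conclusion.** The point holds as a weakness in the matching rule. The listed criteria do not secure a comparable ward setting, while the outcome is self-reported health on leaving the ward. Neither severity matching nor the planned t-tests close the gap.

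The conclusion rests on the listed criteria being those applied, and on quality of life differing between ward types; the second is plausible but not shown in the article. Bias further requires the two groups to have different ward mixes. Size and direction are undetermined. The 49% to 75% for mixed pairs is an illustration under ward-blind pairing, not an estimate.

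Three stronger readings should be avoided:

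- The period covered does not differ between patients. It is seven days for everyone, and only its make-up varies.
- Controls are not unrestricted. They come from the same hospital, and participation required an expected stay of at least 48 hours.
- The primary and secondary outcomes are untouched. The six-month survey is also outside the point, since its forms are mailed to patients' homes.

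This is a worthwhile improvement to one nested comparison.

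**What to change.** Add ward type to the matching criteria of the quality-of-life study, as the cost study already does. Where a positive patient has no control from the same ward type, keep the pair and adjust the paired comparison for ward type.

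Do not match on length of stay. Instead, report a sensitivity analysis that adjusts the paired difference for hospital days within the seven-day window, and state that this adjustment may absorb part of any effect acting through a longer stay.

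The cost is small. Admission and discharge data are already on the documentation sheet, and ward type is needed for the cost study, so no new data collection is required. The downside is that a few positives may lack a same-ward-type match, most likely in the smaller hospitals. The number of such pairs should be reported.
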